### Recruitment {15}

Evidence-based site selection was used to confirm the eligibility of each centre to participate in the trial using volumes of endovascular repair of infra-renal and thoraco-abdominal aortic aneurysms listed on the National Vascular Registry as well as a record of satisfactory patient outcomes and strong clinical engagement. During the trial, the team will maintain regular contact with the sites, undertake regular site visits, and ensure there are adequate numbers of randomisers at sites and that Cydar EV is installed in as many rooms as required. These will be supplemented by in person local principal investigator and research nurse meetings where site teams can hear the experience of other sites and problems and tips and tricks to ensure strong participant recruitment can be shared.

## Assignment of interventions: allocation

### Sequence generation {16a}

Once baseline assessments are complete, participants will be randomised in a 1:1 ratio using the method of minimisation. Randomisation is at the patient level and is performed using a web-based bespoke randomisation system set up by the King’s Clinical Trials Unit (KCTU) at King’s College London. Randomisation is minimised by the following factors:SurgeonProcedure urgency: emergency or electiveProcedure type: simple (repair of infra-renal aneurysm ± internal iliac embolisation) or complex (all other types of AAA and TAAA repair, to include branched and fenestrated devices)

The procedure is as follows: on receipt of the baseline questionnaire, the trial coordinator electronically submits details of each participant to the CTU. This includes participant ID number, site, initials, and date of birth. The system immediately notifies the relevant study nurse and records the randomisation outcome. The trial coordinator does not receive the randomisation outcome.

### Concealment mechanism {16b}

Minimisation will incorporate a random component to assure allocation concealment.

### Implementation {16c}

Patients will be enrolled in the ARIA trial by the local trial team at each of the participating sites as per the described consenting procedure. The allocation sequence generation will be implemented via the Kings College Trial Unit (KCTU) web-based randomisation system. The randomisation of participants will be performed post-consent, after checking their eligibility. The signed consent form will be made available for the operating team to review, along with the randomisation result. Participants will be randomised to Cydar-EV image fusion for guidance or standard imaging techniques in a ratio of 1:1 post-consent and confirmation of eligibility.

### Randomisation procedure

Study site staff delegated to undertake the randomisation procedure will generate a unique patient identification number (PIN) using the Elsevier MACRO EDC system and randomise the patient using the KCTU web-based randomisation system.

## Assignment of interventions: blinding

### Who will be blinded {17a}

Due to the nature of the intervention, it is not possible to blind all members of the trial team. Table 1 lays out the blinding status of the research team in this study.

**Table 1 Tab1:** Blinding status of research team

**Individual blinding status**	**Blinded**	**Unblinded**
Chief investigator	**X**	
Principal investigators at site		**X**
Trial manager/monitor		**X**
Senior statistician	**X**	
Junior statistician		**X**
Independent image reader	**X**	
Cydar project manager		**X**
Trial participants		**X**
Outcome assessors/research nurses		**X**
Treating clinicians		**X**
Trial steering committee (TSC)	**X**	
Data monitoring committee		**X**

### Procedure for unblinding if needed {17b}

Emergency unblinding is not required in this study.

## Data collection and management

### Plans for assessment and collection of outcomes {18a}

#### Source data worksheets

Sites will be provided with source data worksheets containing the relevant data required to be transcribed to the MACRO EDC system and the randomisation system. Training will be provided by the ARIA trial manager.

#### CT aorta image reading

CT imaging data will be uploaded to the ARIA trial image analysis virtual CoreLab, which is a cloud-based system. Images will be read in a blinded manner by two readers, with more than 5 years of experience of aortic image analysis and with experience of aortic endovascular surgical planning. They will securely log into the cloud-based Cydar vault where the CT image data will be housed and analyse the pre- and post-operative CTs to determine technical success. Data from this analysis will be entered onto a part of the MACRO EDC system inaccessible to sites. Twenty image data sets will be used to assess the inter- and intra- observer repeatability coefficients for the variables in the CT read protocol.

#### Plans to promote participant retention and complete follow-up {18b}

Participants will be seen in routine NHS follow-up clinics. If visits have not been scheduled by the end of the week 4–12 and week 52 visit windows, the study site staff will contact the participants by telephone to collect the EQ-5D (telephone version) and follow-up data, and attempts will continue to schedule a follow-up visit. Data will be collected and entered, even if follow-up clinic assessments are outside the optimal visit windows and the date noted.

### Data management {19}

#### Data entry

Authorised staff at sites will transcribe baseline and follow-up data from the source data worksheets. A full audit trail of data entry and any subsequent changes to entered data will be automatically date and time stamped, alongside information about the user making the entry/changes within the system.

#### Security (EDC)

Systems access will be strictly restricted through user-specific passwords to the authorised research team members. Participant initials and partial date of birth (mm/yyyy) will be entered into the systems. Hospital number, email address, participant names and addresses, and full postcodes will not be entered into the EDC system. Trial sites will maintain a master patient log linking participant identifiers to study numbers. No data will be entered unless a participant has signed a consent form to participate in the trial.

#### Data quality processes

At the database design stage, validations will be programmed into the systems to minimise data entry errors by querying the data entered in real time with sites. The CI team will undertake appropriate reviews of the entered data, in consultation with the project analyst, where appropriate for the purpose of data cleaning and will request amendments to the MACRO EDC system data as required. No data will be amended independently of the study site responsible for entering the data. No data can be amended in the randomisation system; however, CI or delegate (e.g. trial manager) may request King’s Clinical Trials Unit to add notes against individual participant entries to clarify data entry errors. Any errors should be reported by site staff to the trial manager as soon as possible once they are detected. The trial manager will onward report errors to KCTU and retain records in the TMF. Site monitoring visits will be conducted by the trial manager.

### Confidentiality {27}

When consent forms are signed, a copy will be provided to the patient, a copy will be filed in the medical records, and the original will be retained in the Investigator Site File. Participant initials and date of birth will be entered into the study database, but no more identifying information will be collected outside the recruiting study site. Within site, an Investigator Site File will be maintained by the site PI. Participants will be fully identifiable within these files.

### Plans for collection, laboratory evaluation, and storage of biological specimens for genetic or molecular analysis in this trial/future use {33}

There are no biological specimens that will be taken as part of this trial.

## Statistical methods

### Statistical methods for primary and secondary outcomes {20a}

The analyses will be carried out according to the statistical analysis plan written before any outcome data are inspected. A CONSORT diagram will describe the patient flow and exclusions. Baseline demographic and clinical data will be summarised by randomisation trial arm.

#### Statistical methods for primary outcome

As the primary outcome is procedure duration and we envisage 7.5% loss of patients between randomisation and procedure, the primary analysis will be a per-protocol (PP) analysis based on procedure time. The primary analysis will be conducted after completion of first follow-up (at 4–12 weeks) which will include procedure time as well as the secondary outcome data available at this time. Sensitivity analysis with multiple imputation for missing data will also be conducted alongside the per-protocol analysis. No significance tests will be performed for baseline comparison. The primary outcome measure is likely to have a skewed distribution and therefore if necessary and possible the data will be normalised using an appropriate transformation. The data will then be analysed using linear regression techniques with stratification (minimisation) factors included as covariates. If a suitable transformation cannot be found, the data will be analysed using quantile regression to allow us to include the addition of the stratification factors as covariates.

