### Eligibility criteria {10}

Below are the inclusion and exclusion criteria of the ARIA trial.

Inclusion criteria:Clinical diagnosis of AAA or TAAA suitable for endovascular treatment, as determined by CT imaging and a local treating team multidisciplinary reviewPatient is confirmed fit for endovascular repair as determined by the operating teamCT imaging must be in accordance with Cydar EV: Instructions for UseWritten informed consent (patients lacking capacity or unable to speak English will not be enrolled)Age 18 years and above at the time of consent

Exclusion criteria:Patients unable to provide written informed consent

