### Sample size {14}

There is no known minimum clinically important difference (MCID), and part of the aim of the study is to better characterise the clinical benefit to patients. The study is therefore powered on the basis of a minimum economically meaningful difference. Previous work at Duke [9] reported data on the primary outcome, procedure time, and found a mean difference of 22.5 min (17%) for patients with an abdominal aortic aneurysm treated with Cydar-EV 109.6 (34.2) and standard 2D fluoroscopy imaging 132.1 (69.2) minutes. This is a meaningful difference in the NHS context as this time reduction per case would allow four rather than three EVAR procedures to be performed per day, which is a productivity increase of 33% at the same capacity. The SD for procedure time increases with the mean and so we have assumed a *t*-test for ratio of means 1.2 (fold change), assuming a lognormal distribution for the calculations. Therefore, a sample size of 153 patients per arm with a 1:1 allocation ratio (2 × 153 = 306) would give us 90% power at the 2-sided 5% significance level to detect this difference (PASS 15 Power Analysis and Sample Size Software (2017)). Since our primary outcome measure requires the procedure to be completed, we need to inflate the sample size for possible: (i) loss post randomisation, pre-procedure (est. 7.5%), and (ii) on-table death and cross-overs (where surgeons may use the intervention in a control arm patient and additional assistance is required to complete the operation) (est. 2.5%). These inflate the sample size to 170 per arm. The final randomisation target is therefore 2 × 170 = 340. The Duke data also showed using Cydar-EV in TAAA showed larger reductions in operating time than for AAA. We have powered on the more conservative difference since the relative proportions of AAA/TAAA patients anticipated in our proposed trial is unknown.

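### The complex procedure class pools complex AAA with TAAA repair, so adding the diagnosis known at entry as a covariate is a free, probably modest, gain in precision

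*Protocol article*

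**What the plan says.** The section on statistical methods for the primary outcome names the covariates by reference: "The data will then be analysed using linear regression techniques with stratification (minimisation) factors included as covariates". If no transformation works, quantile regression is used with the same factors. The secondary-outcome section says a similar analysis will follow.

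Sequence generation {16a} lists three minimisation factors: surgeon, urgency (emergency or elective) and procedure type (simple or complex). Simple means infra-renal repair, with or without internal iliac embolisation. The other level is "complex (all other types of AAA and TAAA repair, to include branched and fenestrated devices)".

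The first inclusion criterion in Eligibility criteria {10} is "Clinical diagnosis of AAA or TAAA suitable for endovascular treatment, as determined by CT imaging". Implementation {16c} places randomisation after the eligibility check, so the diagnosis is known by then. It is neither a minimisation factor nor a named covariate.

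Sample size {14} separates the two diagnoses: "The Duke data also showed using Cydar-EV in TAAA showed larger reductions in operating time than for AAA". It adds that their mix in this trial is unknown, and it takes its planning means and SDs from AAA patients.

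**The concern.** The two-level procedure type separates every TAAA from simple infra-renal AAA repair, but does not separate TAAA from complex AAA repair. If TAAA repair takes longer than complex AAA repair, that difference is explainable variation that the stated model leaves in the error term, except for the part that surgeon or urgency picks up. Minimisation does not balance it directly either.

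What is at stake is precision: a wider interval for the treatment ratio, and some of the planned 90% power. The planning SD comes from AAA patients while TAAA patients are eligible, so any extra spread between the diagnoses may not be in that SD. The same covariates would carry over to anaesthetic duration, X-ray dose and contrast dose.

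**Working it through.** **Inputs from Sample size {14}.** The trial "would give us 90% power at the 2-sided 5% significance level to detect this difference"; the effect is a "ratio of means 1.2 (fold change), assuming a lognormal distribution for the calculations"; the data are AAA patients "treated with Cydar-EV 109.6 (34.2) and standard 2D fluoroscopy imaging 132.1 (69.2) minutes"; the result is "a sample size of 153 patients per arm with a 1:1 allocation ratio".

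**1. The plan's own figure.**
- Control CV = 69.2/132.1 = 0.524. Log variance = ln(1 + 0.524²) = 0.2425, so log SD = 0.492.
- Target on the log scale: ln(1.2) = 0.1823.
- n per arm = 2 × 0.2425 × (1.960 + 1.282)² / 0.1823² = 153.3. This rounds up to 154 (155 with the t distribution).
- Power at 153 per arm is 89.9% (89.8% with the t distribution).

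The stated 153 is therefore reproduced, from the control-arm SD alone.

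**2. Variance left in by the pooled class.** Let p be the complex share of all patients, q the TAAA share of complex patients, and R the ratio of TAAA to complex AAA duration. After adjustment for simple/complex, the residual still contains

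v = p × q × (1 − q) × (ln R)².

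The protocol gives none of p, q or R. The ranges used are assumptions: p 20–60%, q 20–50%, R 1.25–2.0.

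**3. Power at 153 per arm without the covariate, taking 0.2425 as the within-diagnosis log variance.**

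| Case | p, q, R | v | Total log variance | Power | n per arm for 90% |
|---|---|---|---|---|---|
| Mildest | 0.20, 0.20, 1.25 | 0.0016 | 0.2441 | 89.8% | 155 |
| Mid | 0.40, 0.35, 1.5 | 0.0150 | 0.2574 | 88.2% | 163 |
| Extreme | 0.60, 0.50, 2.0 | 0.0721 | 0.3146 | 81.1% | 199 |

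Mid-case substitution: 0.40 × 0.35 × 0.65 × (ln 1.5)² = 0.091 × 0.1644 = 0.0150, which is 5.8% of the total variance.

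**4. If 0.2425 already contains v.** Adding diagnosis then raises power above 89.9%: to 90.1%, 91.7% and 97.1% in the three cases.

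**5. If both arms' SDs are used.**
- Cydar-EV CV = 34.2/109.6 = 0.312, so log variance = 0.0929.
- Two-arm average: (0.2425 + 0.0929)/2 = 0.1677, with power of 97.3% at 153 per arm.
- Adding v gives 0.1827 in the mid-case (power 96.2%) and 0.2398 in the extreme case (power 90.3%).

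Even the extreme total lies below the 0.2425 that produced 153 per arm.

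**6. Chance imbalance.** In the mid-case, the SD of the between-arm difference in TAAA share is √(2 × 0.091/153) = 0.034. Multiplied by ln 1.5 this is 0.014 on the log scale, and a 1.96-SD imbalance moves the ratio by a factor of 1.028. Over the ranges the factor runs from 1.009 to 1.062. This is not an additional cost: 0.014² equals 2v/153 = 2 × 0.0150/153, the same variance already charged in step 3.

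**The case against.** The strongest reply is that adjusting for all the minimisation factors is a standard and valid analysis, that the unseen SAP may add prognostic covariates, and that nothing in the primary-outcome section forbids them. That stands as a defence of validity. It does not remove the suggestion, because the protocol states a covariate set and that set omits a relevant variable already known at entry.

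It also stands that the power figures in step 3 are unfavourable to the plan. They use the larger arm's SD, treat an unadjusted SD as the residual SD, and give no credit for what surgeon, urgency and simple/complex explain.

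Three stronger readings are tempting, and the document supports none of them.

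- **Diagnosis is known to drive procedure time.** The Sample size section reports a larger reduction with Cydar-EV in TAAA. That is a difference in treatment effect, not in baseline duration, and no duration contrast between TAAA and complex AAA is given anywhere. A main-effect covariate would not address a difference in treatment effect.
- **A chance imbalance in TAAA share biases the estimate.** Under randomisation the standard error already covers it, and step 6 shows that it is the same variance counted again.
- **The per-protocol analysis turns this into bias**, because cross-over runs only from standard care to Cydar-EV, in very long procedures or for patients in extremis. This needs TAAA patients to be over-represented among those cases, which the document does not say. It estimates on-table deaths and cross-overs together at 2.5%. Any such bias would come from the choice of analysis set.

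**Conclusion.** The point holds as an optional improvement in precision. The primary model adjusts for surgeon, urgency and procedure type. The one contrast it leaves out is TAAA versus complex AAA inside the complex class. The test remains valid and the estimate is not biased by the omission.

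The size is unknown and probably modest. With the control-arm log SD taken as the within-diagnosis SD and the assumed ranges for mix and duration ratio, power at 153 per arm lies between about 81% and 90%, with a mid-case near 88%. The low end needs complex repair to be common, half of it TAAA, and TAAA to take twice as long as complex AAA. With both arms' published SDs, power does not fall below 90% anywhere in those ranges. The case for acting is that the change is almost free, not that the trial is shown to be underpowered.

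**What to change.** Before any outcome data are inspected, pre-specify AAA versus TAAA diagnosis as a covariate in addition to surgeon, urgency and procedure type. Equivalently, replace the two-level procedure type in the model with three levels: simple, complex AAA and TAAA. Apply this to the primary model, including the quantile-regression fallback, and to the models for anaesthetic duration, X-ray dose and contrast dose.

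Take the diagnosis from the pre-randomisation CT used for eligibility, not from the final operative plan: Cydar-EV includes planning tools, so the plan could be affected by allocation.

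The cost is one sentence in the SAP and one degree of freedom. It needs no new data and no change to the minimisation or to the sample size.

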#### Statistical methods for secondary outcomes

A similar analysis will be undertaken for the secondary outcomes including quality of life scores. Binary outcomes will be compared between arms using logistic regression adjusting for stratification factors. Outcomes will be reported as adjusted differences in means (or median) or odds ratios for continuous and binary data respectively. All tests will be two sided and will be assessed at the 5% significance level. Safety outcomes will be reported as patient proportions and rates within and between arms with 95% confidence intervals using exact methods where appropriate.

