#### Intervention delivery

Procedures will be performed under local, regional or general anaesthesia (likely ratio: 1:1:8). Procedures can be undertaken using either a mobile C-arm in a surgical operating theatre, a dedicated fixed fluoroscopy set, or in a hybrid operating room. Patients may go to the ward, HDU, or ICU following the procedure, according to local protocol. Routine pre-operative CT aortic imaging will be used to determine general suitability for endovascular repair, including assessment of landing zones for fixation and sealing, and procedure type and device selection.

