#### Secondary outcomes

Procedural efficiency:Anaesthetic duration—the time between the beginning of induction and the end of emergence. This will be documented at the time of the procedure by the local research team in minutes.X-ray dose per procedure—fluoroscopy time (FT) (seconds), dose area product (DAP) (Gy.cm2) and cumulative air kerma (CAK) (mGy) should be recorded and documented at the time of the procedure by the local research team. The imaging system used should also be recorded.Contrast dose per procedure—the volume (ml) and concentration (mgI/ml) of the iodinated contrast material used should be recorded by the local research team at the time of the procedure in minutes.Consumable use in the operating theatre for endovascular aortic aneurysm repair—name of device, unit and quantity used, blood products used; details to be completed by nurse in the operating theatre or research nurse at the time of the procedure.Technical success:Proximal and distal seal zone at least 10mm and no evidence of endoleak. This will be documented by the imaging CoreLab team on review of the CT images acquired post-operatively and at 4–12 weeks and at 52 weeks.Patient outcomes:Length of ICU/HDU admission—date and time from admission to date and time of discharge from ICU/HDU; documented by the local research team during the time of admission; ICU and HDU admissions should be documented separatelyPostoperative length of hospital stay—date of procedure to date of discharge from hospital (nights); documented by the local research team during the time of admission.30-day mortality—death of the participant within 30 days of the primary procedure; documented by the local research team; to include date of death (dd/mm/yy) and cause.Re-intervention—any procedure open surgical or endovascular undertaken within 1 year of the primary endovascular aortic aneurysm repair procedure (binary outcome). The type, timing, and number of procedures should also be recorded by the local research team.Adverse events—hospitalisation for any reason within one year of the primary endovascular aortic aneurysm repair; the type of event should be documented and classified as one of the following: musculoskeletal, urological, neurological, ophthalmological, cardiovascular, gastro-intestinal, hepato-pancreato-biliary, dermatological, or other by the local research team, with information captured to understand if linked to re-intervention. For each hospitalisation, the following should also be captured:i.Day case, elective, non-electiveii.Length of hospital stay—date of admission to date of discharge (nights)iii.Length of ICU/HDU admission (if applicable)—date and time from admission to date and time of discharge from ICU/HDUQuality of life—differences in quality of life between intervention and the comparator group and changes in quality of life post-surgery will be measured using data from the patient-completed EQ5D-3L [11] instrument. EQ-5D-3L is a validated measure of health-related quality of life, consisting of a five-dimension health status classification system and a separate visual analogue scale. EQ-5D-3L data will be obtained through face-to-face or telephone interview with the participant at baseline, pre-discharge, 4–12 weeks, and at 12 months follow-up.Cost-effectiveness, as assessed by:Total resource use and costsQuality-adjusted life years (QALYs)—quality of life will be measured by the EQ-5D-3L instrument as described above. In order to be used in the calculation of quality-adjusted life years (QALYs), the EQ-5D-3L dimension scores will be converted to utilities using the relevant value set for England. Quality-adjusted life years (QALYs) gained in both groups, over the time horizon of the trial, will be calculated using the area under the curve method.Incremental cost per QALY

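### The carried-over rule fits ICU and HDU length of stay badly: if clearly more than half of patients have no such stay, it is likely to report an uninformative median difference of zero

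*Protocol article*

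**What the plan says.** The protocol article sets a two-step rule for procedure time under Statistical methods for primary outcome. First, "if necessary and possible the data will be normalised using an appropriate transformation", followed by linear regression on arm and the minimisation factors. Second, "If a suitable transformation cannot be found, the data will be analysed using quantile regression", with the same factors as covariates.

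Statistical methods for secondary outcomes extends this: "A similar analysis will be undertaken for the secondary outcomes including quality of life scores". Binary outcomes are sent to logistic regression, and safety outcomes are summarised as proportions and rates. Nothing exempts durations of stay. On reporting: "Outcomes will be reported as adjusted differences in means (or median) or odds ratios".

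Secondary objectives lists ICU stay and HDU stay as two items. The Secondary outcomes section defines them thus: "Length of ICU/HDU admission—date and time from admission to date and time of discharge from ICU/HDU", with the two units recorded apart. It assigns no value to a patient who never enters the unit. Intervention delivery says: "Patients may go to the ward, HDU, or ICU following the procedure, according to local protocol". The article gives no share of patients for any of the three destinations.

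**The concern.** Procedure time is positive and right-skewed, so transforming it, or modelling its median if that fails, is reasonable. Stay in a unit that some patients never enter is different: a block of exact zeros plus a skewed positive part. A monotone transformation moves the block but cannot spread it out, and a plain log is undefined there. Taken literally, the rule therefore ends at quantile regression. The reporting sentence mentions a median, so this would mean median regression.

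If most values are zero, the median is zero in both arms whatever the device does to the chance of admission or to the length of longer stays. A published median difference of zero could then be read as no effect on critical-care use, while the economic analysis, which needs means, shows one.

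Leaving out patients who were not admitted removes the zeros. But admission happens after randomisation and may itself depend on the treatment, so the comparison would no longer be between randomised groups.

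**Working it through.** **Trial size used.** The article gives no figure for ICU or HDU stay. Its one computed figure is the primary sample size (Sample size {14}): 153 per arm, which "would give us 90% power at the 2-sided 5% significance level" for a ratio of means of 1.2 under a lognormal model. With the control-arm figures, CV = 69.2/132.1 = 0.524 and log-variance = ln(1 + 0.524²) = 0.2425. Then n = 2 × 0.2425 × (1.960 + 1.282)² / (ln 1.2)² = 153.3, so 154 per arm. Power at 153 is 89.9%, and 153/0.9 = 170. The stated figures are reproduced, and 153 per arm is used below.

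**How many zeros?** The share is not stated. Let w be the share using neither unit and s the share using both. Then ICU share + HDU share = 1 − w + s, so the less-used unit is used by at most (1 − w + s)/2 of patients, and its zero share is at least (1 + w − s)/2.

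- One destination each (s = 0): at least 50% zeros in one of the two outcomes, and more if anyone goes to the ward.
- Assumed 20% moving from ICU to HDU (s = 0.20, w = 0): the bound falls to 40%.
- Assumed 30% (s = 0.30, w = 0): it falls to 35%.

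**Unadjusted illustration (assumed values).** Suppose the same share is admitted in both arms and mean stay among those admitted is 36 v 24 h. At 30% admitted, the mean difference over all patients is 0.30 × 36 − 0.30 × 24 = 3.6 h. At 10% it is 1.2 h and at 40% it is 4.8 h. The unadjusted median difference is 0 in each case.

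**Adjusted analysis, by simulation.** Each scenario had 100 trials of 153 per arm, with a point mass at zero plus a lognormal stay. A real effect was built in: stays 20% shorter on treatment and, except in the scenario with about 10% zeros, more zero stays. Median regression was on arm, procedure type and urgency (surgeon omitted). With 100 trials the simulation standard error is at most √(0.25/100) = 5 percentage points.

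| Zeros unrelated to covariates | Difference exactly 0 | Zeros related to procedure type and urgency | Difference exactly 0 |
|---|---|---|---|
| 10% | 0% | 12% | 0% |
| 35% | 0% | 35% | 9% |
| 50% | 3% | 48% | 90% |
| 55% | 52% | 52% | 97% |
| 65% | 100% | 60% | 99% |
| 75% | 100% | 68% | 100% |
| 93% | 100% | 88% | 100% |

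Median regression returned an estimate in every scenario, although the iterative fitting routine often reached its 300-iteration limit. Its standard error collapsed to about zero or was undefined in 40% of trials at 75% zeros (no covariate effect), and in all trials at about 88–93%. Linear regression of log(1 + stay) always fitted and rejected the null in 23–69% of trials, so the effect was not beyond detection. That transformation still leaves the spike in place.

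**The case against.** The strongest reply is that the article does not fix a rigid recipe. It refers to a separate analysis plan, not shown, written before outcome data are inspected. The secondary analysis need only be similar, transformation is conditional, and mean differences are allowed. An adjusted mean difference could therefore be reported without contradicting the article. This stands in part, and it is why the point is put as a likely result rather than a certain one. It does not dispose of it. The stated order is to normalise and otherwise use quantile regression, and zero-heavy stays fail the first step. Nothing in the article directs the analyst back to means.

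A reader might go further than the documents allow in four ways:

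- **That many patients will have zero stay.** No shares are given. With 35% or fewer zeros, an exact zero difference was unusual.
- **That at least one outcome must be at least half zeros.** This needs one destination per patient. The article does not say destinations are exclusive, and ICU-to-HDU step-down lowers the bound.
- **That any admission share below 50% forces a zero result.** This is exact for unadjusted medians only. In the adjusted analysis at 55% zeros unrelated to covariates, it occurred in 52% of trials.
- **That the model cannot be fitted.** Estimates were always obtained. What fails is the plain log, which the article does not prescribe for these outcomes, and the standard error at high zero shares.

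Nor does anything say that costs will be built from a median difference. The health economic analysis is separate.

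**Conclusion.** The point holds in conditional form. The article states a rule and carries it to two outcomes whose likely shape it does not suit. If clearly more than half of ICU or HDU stays are zero and all analysed patients are included, the adjusted median difference is likely to be zero whatever the treatment effect. This was near certain from about 60% zeros. Around 50% it varied with how zeros relate to procedure type and urgency: 3% of trials at 50% zeros, against 90% at 48%. Standard errors become unreliable at very high zero shares.

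This rests on three assumptions: non-admitted patients count as zero, the rule is followed in its stated order, and the zero share is high. The documents settle none of them. If stay is instead analysed in admitted patients only, the zeros disappear but so does the randomised comparison. The documents do not support saying that a zero result is built in. The matter concerns two secondary outcomes; the primary outcome and sample size are unaffected.

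**What to change.** In the analysis plan, before outcome data are inspected, except ICU and HDU length of stay from the carried-over rule. For each unit separately:

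- count a patient not admitted to the unit as zero hours;
- report the proportion admitted by arm;
- report the adjusted mean difference in hours over all patients in the analysis, zeros included, from linear regression with bootstrap or robust confidence intervals, adjusted for the minimisation factors as already planned (surgeon, urgency, procedure type).

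These means are also on the scale that the cost analysis needs. The data are already to be collected, so the change is one of wording plus a little more analysis work. The drawback is that means are sensitive to a few very long stays. Showing the proportion admitted beside the mean helps the reader judge that.
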